## Methods/design

### Study design

The study protocol was designed in accordance with the SPIRIT guidelines [38]. This is a 12-week, randomized controlled, parallel-group, multicenter trial of intradialytic NMES and protein supplementation for HD-dependent ESRD patients. Seventy-two patients receiving HD will be randomly assigned in a 1:1:1:1 ratio to the control, intradialytic NMES only, protein supplementation only, and intradialytic NMES combined with protein supplementation groups. Measurements will be scheduled for all patients at baseline and at follow-up every 4 weeks for 12 weeks; the measurements will include vital signs; blood and urine laboratory exams including total protein, albumin, total cholesterol, calcium, phosphorus, blood urea nitrogen (BUN), serum creatinine (SCr), total CO_2_, intact parathyroid hormone (PTH), highly sensitive C-reactive protein (hs-CRP), urine urea nitrogen/normalized protein catabolic rate (nPCR), and Kt/V; and body composition including bioelectric impedance study, physical performances, and questionnaires. Figure 1 presents a flowchart of the trial procedures.

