### Recruitment and population

A total of 72 patients with ESRD receiving HD will be recruited in four tertiary hospitals in Korea.

Subjects will be eligible for inclusion in this study only if all of the following criteria apply: (1) stable ESRD patients who have been receiving HD for 3 months or more, (2) patients with serum albumin less than 4.0 g/dl and are suspicious of having PEW, and (3) patients who can thoroughly understand the protocol.

Subjects will be excluded for any of the following reasons: (1) acute kidney injury; (2) uncontrolled hypertension, diabetes, or heart failure; (3) aspartate aminotransferase (AST) or alanine aminotransferase (ALT) level 3 times or higher than the upper normal limit of the participating hospital; (4) hematologic or solid organ malignancies under treatment; (5) active infection; (6) positive for HIV/AIDS; (7) history of ischemic heart disease, stroke, or deep vein thrombosis within 3 months before participation; (8) planning to receive kidney transplantation within 3 months after participation; (9) contraindication to electronic stimulation including implantable defibrillator; (10) skin lesions around the electrical stimulation spots; (11) allergy to protein supplements; (12) history of participation in another clinical study within 2 months prior to study enrollment and plans to participate in another clinical study; and (13) researcher’s decision regarding inappropriateness of enrollment in the study.

All patients who are eligible for this study will be asked by study investigators. They will receive oral and written information from the investigator. The investigator will obtain written informed consent and the patient will be randomized.

As the participation in the study is voluntary, all participants are free to withdraw their consent to participate in the study at any time and for any reason without any further treatment or any consequences. Moreover, participation of any participants could be terminated by an investigator at any time, if an investigator believes it is in the best interest of the participant. We shall document the reasons and circumstances of the study discontinuation in the clinical record form.

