### Randomization and concealment

The experiment will be conducted by block randomization (block size of 4; stratified block randomization schedule for 4 institutions; each institution has a separate randomization schedule); the blind code will be computer-generated by a statistician of an external organization (Seoul National University Hospital Medical Research Collaborating Center) using SAS®, who had no contact with participants. Only an independent physician assistant at the central coordinating institution will have the pregenerated codes, and all other research members will be blinded. Researchers call a central coordinating office for each patient assignment. Participants will be randomly assigned to the control (random code A), intradialytic NMES (random code B), protein supplementation (random code C), or intradialytic NMES combined with protein supplementation (random code D) for 12 weeks according to their assigned code, after they agree to enroll in the study and sign the informed consent form.

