### Quality control, data management, and monitoring

This study is organized by a team comprised of a principal investigator and co-investigators who take part in the design and implementation of the study. For quality control purposes, all the researchers will be trained to be well-acquainted with the study protocol and to perform tests in one unified way before the recruitment of participants. The interventions will be performed by one expert at each hospital. All data will be put onto a computer with password protection by a staff blinded to the group allocation. The original forms of data will be archived securely at the central coordinating institution. All the investigators will be responsible for data monitoring, which is performed after each subject’s participation is completed. Monitoring includes assessment of the progress of the study and verification of accuracy as well as the completeness of recorded data. After completion of the study, we will submit the original data and results to IRBs of participating institutions, and after the publication of results, we will disclose original data and results to the public. Audits will be held annually by the IRBs of participating institutions.

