### Statistical methods

The statistical processing will be performed with PASW advanced statistics (SPSS Inc, Chicago, IL) version 20.0 and according to an intention-to-treat principle. Data will be reported as the mean, standard deviation, and confidence intervals or in percentage frequencies. The Shapiro-Wilk test will evaluate the normal distribution of the variables. Evaluation variables, including muscle strength, performance tests, and questionnaire surveys, will be analyzed at baseline and after 4, 8, and 12 weeks by using paired *t*-tests or Wilcoxon signed-rank tests. Outcomes will be compared between groups by using two-sample *t*-tests or Wilcoxon rank sum tests according to normality. Analysis of covariance will also be conducted. The between-group differences in the outcome measures after the intervention will be calculated using repeated measure mixed models with patients as random effects, and group and time as fixed effects, and adjustments for baseline imbalances. The Spearman rank test or Pearson product-moment correlation coefficient analysis may be used to analyze the associations between clinical data and outcome measures. Statistical significance is set at a *p* value < 0.05. There is no plan for any interim analysis or stopping data collection. There are no planned subgroup analyses for any of the primary or secondary outcomes.

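### The mixed model omits the stratification factor (institution) and ties baseline adjustment to imbalance; prespecifying both covariates would recover power at almost no cost

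*Protocol article*

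**What the plan says.** The Randomization and concealment section describes permuted blocks within institution: "block size of 4; stratified block randomization schedule for 4 institutions; each institution has a separate randomization schedule". The Study design section states "Seventy-two patients receiving HD will be randomly assigned in a 1:1:1:1 ratio", which is 18 per arm, and the Recruitment and population section says that patients "will be recruited in four tertiary hospitals in Korea".

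The Statistical methods section names three kinds of between-group analysis:
- Unadjusted tests: "Outcomes will be compared between groups by using two-sample" t-tests, or rank sum tests, depending on normality.
- Covariance analysis: "Analysis of covariance will also be conducted", with no covariates named.
- A repeated-measures mixed model for the differences after the intervention, "with patients as random effects, and group and time as fixed effects, and adjustments for baseline imbalances".

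Only the mixed model has its terms written out. Institution is not one of them, and no baseline variable is named.

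**The concern.** Two features of the written-out model work against the design.

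**Institution.** Stratified blocks balance the arms within each institution, so differences in level between institutions largely cancel from the group contrast. A model without institution still counts that variance in its error term. The patient random effect does not help: it absorbs the site variance into between-patient variance, which is the yardstick for the group effect. The standard error then overstates the real uncertainty.

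**Baseline.** Baseline strength belongs in the model because it predicts later strength, whether or not the arms look uneven. Read as written, the clause makes adjustment depend on what the data show, with no criterion and no named covariate. Where baseline looks balanced, which is the usual case under randomisation, the precision it offers is given up.

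With a trial sized at 13 completers per group for 80% power, avoidable loss of precision matters.

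**Working it through.** **Inputs from the article (Sample size).** Difference 26.1 − (−8.3) = 34.4; SD 24.82; two-sided alpha 0.0083 (0.05/6); power 80%; 13 completers per group; 25% dropout; 72 recruited.

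**Assumptions, not given in the article.** ICC 0 to 0.30; correlation of baseline with week-12 strength 0.5 to 0.8; a 0.8 SD difference for the baseline comparison; and, for imbalance-driven adjustment, a trigger of p < 0.05 on the baseline difference.

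**Step 1: the plan's own figure.** n = 2 × (24.82/34.4)² × (2.640 + 0.842)² = 12.6, so 13 per group. Then 13/0.75 = 17.3, so 18 per group, and 4 × 18 = 72. The stated figures reproduce. This is an unadjusted two-group calculation with d = 34.4/24.82 = 1.386.

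**Step 2: standard error when institution is omitted.** Take 18 per arm as 5, 5, 4 and 4 blocks, with total variance 1. The share of site variance left in the pooled error is (18/17) × [1 − (25 + 25 + 16 + 16)/324] = 0.791. The ratio of reported to correct standard error is √{[(1 − ICC) + 0.791 × ICC]/(1 − ICC)}:
- ICC 0.10: √(0.979/0.900) = 1.04
- ICC 0.20: √(0.958/0.800) = 1.09

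Simulation gives the same ratios, 1.044 and 1.093.

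**Step 3: level and power for institution.** Four-group model, 13 per arm spread 4/3/3/3 over the sites, d = 1.386, nominal 0.0083, 20,000 simulated trials:

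| ICC | Level without site | Level with site | Power without site | Power with site |
|---|---|---|---|---|
| 0 | – | – | 77.5% | 77.3% |
| 0.10 | 0.0066 | 0.0086 | 80.1% | 83.0% |
| 0.20 | 0.0045 | 0.0084 | 81.2% | 87.4% |

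A separate two-arm simulation at 18 per arm gave levels of 0.0058 and 0.0048 without site at ICC 0.10 and 0.20, and 0.0084 to 0.0090 with site over the whole ICC range. Power without site rises with ICC only because total variance is held at 1.

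**Step 4: baseline adjustment.** 18 per arm, 0.8 SD, alpha 0.05. Unadjusted, the noncentrality is 0.8 × √(18/2) = 2.40. Always adjusting divides this by √(1 − ρ²), giving 2.77, 3.36 and 4.00 for ρ = 0.5, 0.7 and 0.8. Simulated power:

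| ρ | Never adjust | Adjust only if imbalanced | Always adjust |
|---|---|---|---|
| 0.5 | 64% | 65% | 76% |
| 0.7 | 64% | 66% | 89% |
| 0.8 | 64% | 67% | 97% |

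Repeat runs put the figure for always adjusting at ρ = 0.5 between 74% and 76%. The level under the imbalance rule was 0.043, 0.034 and 0.032, so that rule is conservative too.

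**The case against.** **The article is condensed and the analysis plan is not shown.** This stands for the covariance analysis. A reader might infer that institution enters no analysis at all, but its covariates are unnamed and may include institution and baseline. It does not stand for the mixed model, whose terms are listed.

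**The baseline clause may simply mean baseline adjustment.** It states no test or threshold, so a data-driven rule is one reading, not a declared procedure. If plain adjustment is meant, no power is lost and the change only clarifies the wording.

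**Why would sites differ?** A reader might point to the Quality control section: "The interventions will be performed by one expert at each hospital". That does not support this point. Controls receive no intervention, so an operator effect would fall on treated arms and act as site-by-treatment variation, which a site main effect does not correct. With such variation in the NMES arms only (assumed variance 0.10 and 0.20), the level at nominal 0.0083 was 0.0130 and 0.0184 without site, and 0.0137 and 0.0211 with it. The same section also says that researchers are trained to test in a uniform way.

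**The simulations are simpler than the model.** They use one post-baseline measurement. The planning means, one of them negative, look like changes, and stable site differences cancel in changes. Baseline adjustment would also absorb part of any stable site difference. The two gains should therefore not be added, and the site gain may be smaller than shown.

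**Conclusion.** The point holds as an inexpensive improvement to a stated model. It is not a threat to the validity of the results.

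- **Institution.** If sites differ in outcome level, omitting it costs about 3 power points at ICC 0.10 and 6 at 0.20, with tests below nominal level. The ICC is assumed; at 0 there is nothing to gain and about 0.3 points to lose.
- **Baseline.** This is the larger part: about 64–67% power against about 74–97%, for assumed correlations of 0.5 to 0.8, provided the clause means adjustment only when imbalance is seen.

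A reader might infer inflated false positives. Both omissions as simulated are conservative. The level rises to 0.071–0.083 at nominal 0.05 only if an analyst picks the better of the adjusted and unadjusted results, and the article states no such intention.

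**What to change.** In Statistical methods, replace the clause on baseline imbalances in the mixed-model sentence with: *institution (four levels, fixed) and the baseline value of the outcome as prespecified covariates, regardless of observed imbalance*. State that weeks 4, 8 and 12 are the repeated outcomes, so that baseline is a covariate and not also a response.

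Name the same covariates for the covariance analysis. The two-sample t and rank sum tests take no covariates, so label them as supportive.

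The cost is three degrees of freedom for institution and one for baseline. Strength is already measured at baseline and institution is known at randomisation, so no new data are needed and recruitment is unchanged.

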### Dissemination

The study findings will be presented at conferences and reported in peer-reviewed journals.

## Discussion

Sarcopenia occurs early and is more severe in CKD and ESRD patients. Reduced exercise capacity and functional decline due to sarcopenia are important because of their impact on QOL and morbidity [50]. Structural and functional declines in the cardiovascular system and skeletal muscles, which determine exercise capacity and VO_2max_, were less than 75% of the predicted values in CKD patients [31]. Approximately 71% of HD patients had a decrease in quadriceps force that was less than 2 SDs from the average of normal controls [6].

Nutritional support and exercise are the main strategies to prevent and treat sarcopenia. However, malnutrition is common in dialysis patients and many patients are exercise-hesitant.

Insufficient food contributes to PEW and an increased catabolic state, including persistent inflammation, metabolic acidosis, hormonal imbalance, and physical inactivity, leads to excessive muscle wasting [2, 51–53]. Malnutrition is considered a nontraditional cardiovascular risk factor in dialysis patients. Hypoalbuminemia is one of the most potent risk factors for mortality in HD patients [54]. Sarcopenia and low exercise capacity are predictors of morbidity and mortality and show reversed epidemiological tendencies in CKD and ESRD patients [2].

Proteolysis of muscles occurs when proteins or amino acids are required. Continuous and sufficient dietary protein intake is necessary because protein is not stored [11]. Leucine, branched-chain amino acid (BCAA), or β-hydroxy-β-methylbutyrate (HMB) is usually recommended for dietary protein intake in older people. Fast proteins, such as whey protein, may be beneficial compared to slow proteins, such as casein protein [28, 55]. In addition, animal-origin proteins can be better than plant-based proteins at accelerating protein synthesis, if we set aside the control of phosphorus and accompanying conditions in CKD and ESRD patients [28]. We expect protein supplementation including whey protein, as used in this trial, can improve muscle wasting.

Physical inactivity is an important clinical problem among CKD and dialysis patients [27]. Kidney Disease Improving Global Outcomes (KDIGO) recommends fully integrating exercise into the daily activities of CKD patients (≥ 30 min/day, ≥ 5 times/week) to improve cardiovascular fitness and tolerance [56]. The K/DOQI and European guidelines recommend that nephrologists counsel and encourage dialysis patients to increase physical activity [29, 30]. Physicians caring for CKD and ESRD patients should encourage patients to engage in physical activity such as aerobic, resistant, coordination, and flexibility exercises [32]. IDE can be a convenient option to ensure compliance and reduce uncomfortable dialysis-related symptoms such as restless legs and cramping [57]. IDE can enhance or replace physical exercise in frail and exercise-hesitant HD patients. Intradialytic cardiovascular and strengthening exercise improved oxygen uptake, inflammation, arterial compliance, muscle strength, physical activity, and psychosocial functioning. These types of exercise also improved the efficiency of dialysis (Kt/V) and solute clearance, including phosphorus, QOL, depression, and the hospitalization rate [58– 64]. IDE also increased blood pressure in patients with intradialytic hypotension, which has been associated with decreased cardiac output and increased mortality [65, 66]. Regular exercise also showed positive effects on nutritional markers such as serum albumin, prealbumin, and energy intake [27]. In addition, IDE combined with oral or parenteral nutrition enhanced amino acid uptake and protein content in the muscles of HD patients, indicating an improved anabolic effect of nutritional supplementation [67].

However, we often fail to encourage HD patients to perform intradialytic cardiovascular or resistance exercise because patients’ motivation to exercise is lacking. NMES can be a good alternative that can be offered to HD patients. It can be performed just according to the programmed schedule without patient volition. Several studies have proven the effectiveness of NMES in HD patients. However, there has been no research about the effect of simultaneous nutritional support and NMES in dialysis patients.

In summary, we expect that this study can provide guidelines for a new therapeutic option for HD patients who are unable or hesitant to exercise. Furthermore, this option could offer an opportunity to improve the physical function, QOL, and prognosis of HD patients.

## Trial status

The trial is ongoing and is currently recruiting participants. Recruitment was initiated on 26 October 2020 and is expected to be completed by the end of March 2022. The trial is based on a protocol version of 25 August 2019 (1.1). The trial is registered with https://cris.nih.go.kr (Clinical Research Information Service, CRIS), Korea, on 03 November 2020. The last update was posted on 03 November 2020.

## Data Availability

The final trial dataset will be only accessible for the principal investigator on reasonable request.

## Abbreviations

ASM: Appendicular skeletal muscle mass
BCAA: Branched-chain amino acid
CKD: Chronic kidney disease
ESRD: End-stage renal disease
FES: Falls Efficacy Scale
HD: Hemodialysis
HMB: β-Hydroxy-β-methylbutyrate
IDE: Intradialytic exercise
IPAQ: International Physical Activity Questionnaire
KDIGO: Kidney Disease| Improving Global Outcomes
K/DOQI: Kidney Disease Outcome Quality Initiative
KDQOL: Kidney Disease Quality Of Life
KNHANES: Korea National Health and Nutrition Examination Survey
LESM: Lower extremity skeletal mass
NMES: Neuromuscular electrical stimulation
nPCR: Normalized protein catabolic rate
PASE: Physical activity scale for the elderly
PEW: Protein-energy wasting
QOL: Quality of life
SD: Standard deviation
SMM: Skeletal muscle mass
